## Abstract

**Background:**

Physical activity can decrease the risk of complications related to diabetes type 2. Feasible and scalable strategies to implement support for a healthy lifestyle for patients in primary care are needed. The aim of the DiaCert-study is to evaluate a digital healthcare platform and the effect of a 12-week long smartphone-app physical activity intervention aiming at increasing physical activity (primary outcome) and improve levels of HbA1c (glycated hemoglobin), blood lipids, blood pressure, body composition, as well as other lifestyle factors and overall health in patients with diabetes type 2.

**Methods/Design:**

The DiaCert-study is a two-arm, randomized controlled trial that will include 250 patients with diabetes type 2. At baseline, participants are randomized 1:1 to intervention, i.e. use of the smartphone-app, during 12 weeks, or to a control group receiving only standard care. Physical activity and sedentary behavior, is objectively measured using the Actigraph GT3X. Biomarkers including HbA1c and blood lipids are measured in fasting blood samples. Anthropometrics include height, weight, waist circumference and body composition, and a number of lifestyle factors including sleep, diet, self-efficacy, and quality of life, are assessed through an extensive questionnaire. Measurements are made at baseline and at follow-up after 3, 6 and 12 months.

**Discussion:**

Using new technology, is one way to bridge the gap between what patients need and what health care can offer. This study evaluates a new digital health care platform and will show if use of a smartphone-app to promote daily steps is an effective and feasible method to increase physical activity and improve clinical markers in patients with diabetes type 2.

**Trial registration:**

ClinicalTrials.gov Identifier: NCT03053336; 7 Feb, 2017.

## Background

Lifestyle is important in the development of diabetes type 2 and a healthy such may prevent or delay a diagnosis [1, 2]. Nevertheless, globally, the total number of adults diagnosed with diabetes has quadrupled from approximately 100 million in 1980 to more than 400 million today [3]. Additionally, the proportion of adults with unhealthy lifestyles is increasing. In the Nordic countries, almost half of all adults were reported to be overweight or obese, and one third was classified as physically inactive, i.e. not meeting recommendations of moderate-to-vigorous physical activity as defined in the Nordic Nutrition Recommendations 2012 [4], in 2014 [5].

Lifestyle factors, such as overweight or obesity, having an unhealthy diet, or being physically inactive, may also increase the risk of complications from the diabetes. Complications can be serious and may include cardiovascular disease, damage to the kidneys and eyes, feet ulcers leading to amputations, and even premature death [3]. A healthy lifestyle can, on the other hand, decrease the risk of complications related to diabetes type 2. Higher levels of physical activity have been associated with a lower risk of cardiovascular disease, microvascular events, and premature death in patients with diabetes type 2 in observational studies [6, 7].

Early use of technology, such as use of computers, i.e. websites, or mobile phones with short text message services, has been shown to have positive effects on the level of physical activity in patients with diabetes type 2 [8, 9]. However, with the rapid technology development of today, smartphone-applications (apps) are now available for large scale use. Instead, smartphone-apps have been used successfully to improve lifestyle behaviors and clinical outcomes [10]. In Sweden, over 80% of the population own a smartphone and ownership, as well as usage, is independent of socioeconomic status [11]. Use of new technology could be a way to reach large numbers of patients independent on socioeconomic status.

In a review by Schoeppe et al. [10], studies using app-strategies targeting physical activity specifically showed improvements in activity, but although some studies included overweight and/or obese individuals, none included patients with diabetes type 2. Previous studies using app-strategies in patients with diabetes type 2 have mostly focused on glucose monitoring alone, or in combination with lifestyle advice on for example diet and physical activity [12]. Two smartphone-apps that included a physical activity component also included several other components such as, for example, measurement and monitoring of blood glucose, food habits [13], as well as additional monitoring of blood pressure and body weight [14].

Patients with diabetes type 2 are generally taken care of by the primary care and one of the most effective strategies to improve health is regular visits to health clinics [15]. However, this is not a feasible strategy given the large and growing number of patients. New technology, such as eHealth, can be used as an additional strategy to reach patients. eHealth is, as defined by the World Health Organization (WHO), the use of information and communication strategies for health. An additional component of eHealth is mHealth, which has been defined by the WHO as a medical or public health practice that is supported by mobile devices [16]. Mobile devices may include, for example, mobile phones, patient monitoring devices, personal digital assistants, and other wireless devices. Using mHealth strategies, i.e. utilizing the Internet and smartphones, could be one way to bridge the gap between what patients need and what health care can offer. To meet both the needs of patients and the capacity of the health care system, novel ways to implement lifestyle changes are needed.

### Aim

The aim of this paper is to describe the study design and methodology of the DiaCert-study. The main aim of the trial is to evaluate the effect of a 12-week long smartphone-app physical activity intervention aiming at increasing physical activity (primary outcome) and improving levels of HbA1c (glycated hemoglobin), blood lipids, blood pressure, body composition (secondary outcomes), as well as other lifestyle factors and overall health in patients with diabetes type 2.

### Hypothesis

The hypothesis is that the smartphone-app intervention to promote daily physical activity will be effective in increasing physical activity, improving cardiovascular risk factors and other lifestyle factors after 12 weeks of active intervention and long term at 6 and 12 months of follow-up in the intervention group compared to the control group.

## Methods

### Study design and recruitment

The DiaCert-study is a randomized controlled trial with two parallel arms. Patients fulfilling the inclusion criteria are recruited from five primary health care centers around Stockholm, Sweden. Each primary care center volunteered to participate in the study and data collection is performed in collaboration with clinicians and nurses at the centers. Patients that sign up for the study at the health care clinics are contacted by phone. During that contact, patients are given more information about the study. If they fulfill the inclusion criteria and agree to participate they are booked for a meeting in person at which they give their signed informed consent to participate, respond to a lifestyle questionnaire and have baseline measurements taken.

At baseline, study participants are randomized 1:1 to the intervention or control group. All participants, both in the intervention and the control group will continue to receive standard care, i.e. continue their usual care as prescribed by their primary care giver at each participating center, during the whole study period. For participants in the intervention group, the active intervention, i.e. use of the smartphone-app, last for 12 weeks from baseline. All study participants will meet with study personnel at baseline and are followed-up after the intervention at 3 and 6 months, and again after 1 year for assessment of clinical and life style factors. Physical activity is measured using the Actigraph GT3X at baseline and follow-up. For ethical reasons, participants in the control group are offered to use the smartphone-app at the 6-month follow-up if they want. Participants in the intervention group will be offered to download the app again at the same occasion if they wish to start using it again. The study design is outlined in Fig. 1.

**Fig. 1 Fig1:**
[figure not shown]
Flow-chart of the DiaCert-trial study design

The intervention is described according to the CONSORT statement [17] and the CONSORT-EHEALTH checklist developed specifically for eHealth/mHealth interventions [18].

### Inclusion and exclusion criteria

Both women and men are eligible for participation. Inclusion criteria are: having a diagnosis of diabetes type 2, being above the age of 18 years, ability to communicate in Swedish, and having and being able to use a smartphone. Exclusion criteria are: not being able to walk.

### Randomization and blinding

Study participants are randomized to either intervention group (standard care and use of the DiaCert smartphone-app) or control group (only standard care) at baseline at a 1:1 ratio by means of a random allocation sequence list generated in STATA 14.0. Women and men are randomized separately in blocks of ten within each participating primary health care center. Participants are, however, not blind to their allocation due to the nature of the intervention.

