### Sample size and power considerations

Power calculations were performed prior to study start to ensure sufficient power to detect a clinically significant difference in the primary outcome (accelerometer measured physical activity). A total of 200 patients (100 in each group) completing the study would provide sufficient statistical power (80%) at the two-sided 5% significance level to detect a difference in moderate-to-vigorous activity of 8 min/day (e.g. 22 min/day vs. 30 min/day). A standard deviation of ±20 min/day of moderate-to-vigorous activity was assumed in both groups. To cover for a 20% dropout rate (based on earlier intervention studies conducted by our research group), we will recruit 250 patients (125 in each group) to the trial.

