### Statistical analysis

Descriptive statistics will be used to describe characteristics of the study population at baseline. If differences in baseline characteristics are detected, potential confounders will be taken into consideration in further analysis. Data will also be checked for missing values, outliers and normality.

We will summarize pre-specified outcome measures assessed at 12 and 24 weeks of follow-up and compare intervention and control group assessing differences between groups using t-tests, ANOVAs and logistic regression. Analysis will be made following the intention-to-treat approach. Moreover, after completion of the study, follow-up assessment at week 52 will be analyzed within and between intervention and control groups to assess long-term effects. To assess the effect of both time and intervention on the outcomes, trends over time in outcomes will be analyzed using generalized estimation equations. Statistical interaction effects between characteristics and the intervention will also be tested for. Models will be adjusted for unbalanced baseline variables detected. We will also perform analysis stratified on age, sex, BMI, waist circumference, country of birth and primary health care center.

Additionally, results of usage and participants’ opinions regarding usability and satisfaction with the smartphone-app assessed using 16 questions asked at the 3-months follow-up, after the end of the active intervention, will be summarized in the intervention group and investigated in association to baseline factors, using linear and logistic regression.

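### Randomization is stratified by sex and health care center, but the stated tests carry no stratum terms and the adjustment rule would normally leave both factors out; the cost is a mildly conservative analysis

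*Protocol article*

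**What the plan says.** The section on randomization and blinding allocates participants "at baseline at a 1:1 ratio by means of a random allocation sequence list generated in STATA 14.0" and adds: "Women and men are randomized separately in blocks of ten within each participating primary health care center". The section on study design and recruitment says that patients are "recruited from five primary health care centers around Stockholm, Sweden". Allocation is therefore blocked within 2 × 5 = 10 strata.

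The statistical analysis section says the trial will "compare intervention and control group assessing differences between groups using t-tests, ANOVAs and logistic regression", and adds generalized estimating equations (GEE) for trends over time. On covariates it says: "Models will be adjusted for unbalanced baseline variables detected". Sex and center do appear in that section, in the sentence "We will also perform analysis stratified on age, sex, BMI, waist circumference, country of birth and primary health care center". No sentence puts either factor into the main comparison between arms.

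**The concern.** Stratified blocking makes the arms nearly equal in their mix of sexes and centers. Variation between strata then largely drops out of the difference between arm means. An unadjusted t-test does not know this: it estimates its error variance from the total spread, including the part that lies between strata. If the strata predict the outcome, the reported standard error exceeds the real one.

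The adjustment rule makes this more than an omission. It admits variables because they are unbalanced, and blocking is there to keep sex and center balanced. Followed as written, it would normally pass over exactly these two factors.

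At stake are precision and a true 5% level. Intervals would be somewhat too wide, the actual type I error would be below the stated level, and the trial would forgo power that its own design has already made available.

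**Working it through.** **Inputs.** The section on sample size and power considerations gives a difference of 8 min/day ("to detect a difference in moderate-to-vigorous activity of 8 min/day (e.g. 22 min/day vs. 30 min/day"), an SD of 20 min/day in each group, 100 completers per group, 80% power, a two-sided 5% level, 20% dropout and 250 recruited. Strata and block size come from the sections quoted above. R2, the share of outcome variance explained by sex and center, is not in the article. It is an assumption here, varied from 0 to 0.20.

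**The plan's own figure.** n per arm = 2 × (1.960 + 0.842)² × 20² / 8² = 98.1, rounded up to 99. With 100 per arm, power is 0.807 (0.804 by the noncentral t distribution). Dropout: 200 / (1 − 0.20) = 250. The stated sample size reproduces.

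**By formula, assuming perfect balance within strata.**
- t-test SE = 20 × √(2/100) = 2.828, whatever R2 is.
- Real SE under stratified allocation = 2.828 × √(1 − R2).
- Type I error of the t-test = 2 × [1 − Φ(1.96 / √(1 − R2))].
- Power of the t-test = Φ((8/2.828 − 1.96) / √(1 − R2)).
- Power with adjustment = Φ(8/real SE − 1.96).

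| Assumed R2 | Real SE | t-test SE too large by | Type I error, t-test | Power, t-test | Power, adjusted |
|---|---|---|---|---|---|
| 0 | 2.828 | 0% | 5.0% | 80.7% | 80.7% |
| 0.05 | 2.757 | 2.6% | 4.4% | 81.4% | 82.7% |
| 0.10 | 2.683 | 5.4% | 3.9% | 82.0% | 84.6% |
| 0.20 | 2.530 | 11.8% | 2.8% | 83.4% | 88.5% |

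**By simulation, with dropout and incomplete blocks.** Ten equally likely strata, blocks of ten, 250 randomized, 200 completing at random, 6000 runs per setting. The t-test is compared with a linear model that has a term for each of the 10 strata. SE and type I error are from runs with no effect, power from runs with a difference of 8 min/day.

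| Assumed R2 | Mean t-test SE / empirical SD of estimate | Ratio | Type I error, t-test | Type I error, adjusted | Power, t-test | Power, adjusted |
|---|---|---|---|---|---|---|
| 0 | 2.828 / 2.831 | 1.00 | 4.8% | 4.9% | 79.7% | 79.2% |
| 0.05 | 2.826 / 2.757 | 1.025 | 4.5% | 5.0% | 80.2% | 81.4% |
| 0.10 | 2.827 / 2.699 | 1.047 | 4.1% | 5.3% | 81.1% | 83.8% |
| 0.20 | 2.830 / 2.592 | 1.092 | 3.2% | 4.9% | 82.2% | 87.5% |

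The simulation error of a 5% rejection rate is about √(0.05 × 0.95 / 6000) = 0.3 percentage points, and of an 80% power about √(0.80 × 0.20 / 6000) = 0.5 points. The adjusted model's type I error is thus compatible with 5% throughout. The simulated excess in the SE is smaller than the formula gives at the higher R2 values, because incomplete blocks and dropout leave some imbalance within strata. The simulated figures are the ones to use.

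**The case against.** **The text is not closed.** The adjustment rule does not say that imbalance is the only way into a model. Sex and center are named in the analysis section, tests of interaction between characteristics and the intervention are planned, and a condensed article may leave covariate lists to the SAP. This stands in part: a reader cannot conclude that the final analysis will omit the two factors. But the article does more than stay silent. It names the tests and fixes a rule that works against including them. The further analyses by sex and center are introduced as additional and listed beside four factors not used in randomization, so they read as subgroup analyses. These and the interaction tests leave the overall comparison uncorrected.

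**The size is assumed.** This stands. If sex and center predict nothing, the t-test is correct. The discussion section says that the centers serve areas that differ in population and socioeconomic level. That makes a center effect plausible but says nothing about its size for physical activity.

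**The trial's stated claims survive.** This also stands. A reader might infer that ignoring the strata biases the result, inflates false positives or undermines the sample size. The documents support none of these. The error is conservative, and the trial was sized on an unadjusted comparison with the total SD: "A total of 200 patients (100 in each group) completing the study would provide sufficient statistical power (80%) at the two-sided 5% significance level". The t-test still delivers that power. What is lost is lost only against a more efficient model.

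**Adjustment is not wholly free.** This stands, and the costs are given with the remedy.

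**Conclusion.** The point holds as a modest matter of efficiency and correct level. The design stratifies by sex and center, the stated tests do not use the strata, and the stated covariate rule would normally leave them out.

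If the two factors explain 5 to 10% of outcome variance, the standard error is about 2.5 to 5% too large, type I error is about 4.5 to 4.1%, and about 1 to 3 points of power are forgone. At 20%, the standard error is about 9% too large, type I error is about 3.2%, and a little over 5 points of power are forgone. At 0% there is no effect.

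These figures rest on the assumed R2, equally sized strata, dropout unrelated to arm, stratum or outcome, and the article's SD of 20 min/day. The direction, a conservative test when the strata predict the outcome, does not depend on the particular value of R2.

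**What to change.** State in the statistical analysis section that sex and primary health care center enter the main between-group models (linear, logistic and GEE) as prespecified covariates, regardless of observed baseline balance. For outcomes collected at only some centers, such as body composition, which is measured at two, use only the centers that contribute data. The planned analyses by sex and center can remain as subgroup analyses.

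The cost is small but not nil:
- Main effects use 1 + 4 = 5 degrees of freedom; terms for all 10 strata use 9.
- If R2 is 0, about half a point of power is lost (79.7% against 79.2%, simulated with all 10 strata).
- In logistic models the odds ratio becomes conditional on sex and center, and this should be said when it is reported. With 250 / 10 = 25 recruited and 200 / 10 = 20 completing per stratum on average, main effects are likely to be more stable there than terms for every stratum.

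The sample size does not need to change.

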#### Download

The intervention group will download the DiaCert smartphone-app which is connected to a digital platform where the care giver can follow the activity (daily steps) of each individual user. The app is demonstrated and downloaded at the introductory baseline meeting. An individual user account for each study participant is created by the study personnel on the digital platform where data is stored. Unique and temporary 6-digit codes are used to ensure a secure connection to the app for each participant. The individual access codes are created by study personnel and communicated to participants via telephone 7 days after the introductory meeting to avoid overlap with baseline accelerometer measurements. Daily steps measured by the smartphone are thereafter registered and displayed automatically in the app.

After 12 weeks of usage, participants in the intervention group are asked to remove the app from their phones and respond to a short questionnaire including 16 questions about using the app. At the 6-month follow-up, all participants (both in the intervention and control group) are offered to download and connect to the app.

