### Trial status

The first study participants were recruited into the trial in February 2017. Data collection is ongoing with recruitment and baseline assessment planned to continue until a total of 250 study participants have been included or by the end of June 2018, whichever comes first. Follow-up assessments will be complete one year after the last study participant has been recruited.

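### One fixed block size of ten in every center-by-sex stratum of an open trial could let staff who know it and track allocations foresee the end of each block

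*Protocol article*

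**What the plan says.** All statements are in the protocol article.

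- **Sequence (Randomization and blinding).** Allocation is made "at a 1:1 ratio by means of a random allocation sequence list generated in STATA 14.0". The restriction is: "Women and men are randomized separately in blocks of ten within each participating primary health care center". One block size is given, with no mention of variation.
- **Strata (Study design and recruitment).** "Patients fulfilling the inclusion criteria are recruited from five primary health care centers around Stockholm, Sweden". Five centers and two sexes make ten strata.
- **Openness (Randomization and blinding; Download).** "Participants are, however, not blind to their allocation due to the nature of the intervention". For the intervention arm, "The app is demonstrated and downloaded at the introductory baseline meeting".
- **Order of events (Study design and recruitment).** "Patients that sign up for the study at the health care clinics are contacted by phone". Those who qualify and agree are then booked for a meeting at which they consent and are measured, and randomization takes place at baseline. "All study participants will meet with study personnel at baseline".
- **Timing (Trial status).** "Data collection is ongoing with recruitment and baseline assessment planned to continue", up to 250 participants or the end of June 2018, whichever comes first.

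**The concern.** When every block holds exactly ten places, five per arm, an observer who has seen the earlier allocations in a stratum knows how many places remain for each arm. Once one arm's five are used, the rest of the block is known. Concealing the list does not prevent this, because the prediction comes from past allocations that are visible and from a constant block size.

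The sequence of events leaves room to act on such knowledge. Center and sex, and hence the stratum, are known by the time of the phone call, and the patient is booked before being randomized. A keen patient could be booked into a place known to be an app place, or a less keen one held back.

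The primary outcome is physical activity, which plausibly depends on motivation. Baseline adjustment may not fully repair an imbalance in motivation. Under Statistical analysis, adjustment is tied to imbalances that are detected. Under Download, the access code is delayed by seven days so as not to overlap with baseline accelerometry, so baseline activity is recorded after the meeting at which the app is installed.

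**Working it through.** **The plan's own figures.** The article gives no figure for predictability. Its sample size reproduces: 2 × (1.960 + 0.842)² × 20² / 8² = 98.1, so 99 per arm against the stated 100, and 200 / (1 − 0.20) = 250. The point below does not affect it.

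**Inputs.** Block size 2m = 10, so m = 5; ratio 1:1; ten strata; 250 patients. Equal strata of 25 are my assumption, since the article gives no stratum sizes.

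**Certain allocations in a complete block.** The probability that at least the last k allocations are known in advance is 2 × C(10 − k, 5 − k) / C(10, 5), with C(10, 5) = 252.

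| k | Calculation | Probability |
|---|---|---|
| 1 | 2 × 126 / 252 | 1.000 |
| 2 | 2 × 56 / 252 | 0.444 |
| 3 | 2 × 21 / 252 | 0.167 |
| 4 | 2 × 6 / 252 | 0.048 |
| 5 | 2 × 1 / 252 | 0.008 |

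The sum is 1.67, which agrees with 2m/(m + 1) = 10/6. The tenth allocation is always known.

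**Best guess in a complete block.** Guessing the arm that lags behind is right m + (2^(2m)/C(2m, m) − 1)/2 = 5 + (1024/252 − 1)/2 = 6.53 times in 10, against 5 by chance.

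**Over 250 patients.**
- Ten strata of 25: each has two complete blocks and five places of a third. No allocation can be certain before the sixth place, so the count is 10 × 2 × 1.667 = 33.3 (13%). Simulation agrees (33.3) and gives a best-guess rate of 63.5%.
- Every block filled: 25 × 1.667 = 41.7 (17%). This is the ceiling.
- Uneven filling can go slightly below 33. If each stratum stops seven places into its last block, there are 18 complete blocks, and the count is 18 × 1.667 + 10 × (0.008 + 0.048) = 30.6.

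**Varying sizes.** I simulated ten strata of 25 with an observer who knows the set of sizes and keeps every block pattern consistent with the history. An allocation counts as certain when all those patterns allow only one arm.

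| Block sizes | Certain, of 250 | Best guess correct |
|---|---|---|
| 10 only | 33.3 | 63.5% |
| 8, 10, 12 | 4.4 | 63.7% |
| 6, 8, 10 | 4.7 | 65.3% |
| 4, 6, 8, 10 | 3.0 | 66.0% |

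Random sizes remove most of the certainty but do not reduce guessability. Including small blocks makes guessing easier.

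**The case against.** The strongest reply is that prediction needs the same person, or people who share information, to know the block size, to tally allocations by center and sex, and to control who is booked and when. The article does not establish this. It does not say who makes the phone call, who books, or who was told the block size. Separation of roles could close the opening, and such detail commonly sits in the full protocol, which is not shown. This stands, and it is why the point is conditional.

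A reader might infer that recruiters do know the coming allocations, or that selection has already happened. The documents support neither. A reader might also infer that the block size became public while patients were still being enrolled. The article describes recruitment as ongoing at the time of writing, but no publication date is shown, so the number of patients enrolled afterwards is unknown.

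Two further replies stand in part. Ten is a fairly large block for strata of about 25, and it is less predictable than a smaller fixed block (for a fixed block of four, 1.33 of 4 are certain). Baseline accelerometry would also show a marked imbalance in activity. It would not necessarily show one in motivation, and no bias in min/day can be derived from the article to set against the 8 min/day target.

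The reply that this is detail an article may omit does not stand. The block size is a stated rule, and the point concerns that rule.

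**Conclusion.** The point holds in conditional form. A single fixed block of ten, used in all ten center-by-sex strata of an open trial and stated while recruitment is described as ongoing, could let staff who know the size and follow a stratum foresee the end of each block and influence the next booking.

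The size is modest: on average 1.67 of 10 allocations in a complete block, or about 33 of 250 with equal strata. Taking 42 as the expected count would overstate it, because that requires every block to fill. These figures assume full knowledge of past allocations in the stratum. They measure opportunity, not bias. The sample size is unaffected. The point merits action mainly because the remedy is cheap.

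**What to change.** For blocks not yet opened, regenerate the allocation list in the same software, within the same center-by-sex strata, with randomly varying block sizes centered near ten, for example 8, 10 and 12. Do not disclose the sizes to staff who recruit and book. On the equal-strata assumption, certain allocations fall from about 33 to about 4 of 250 even if the set of sizes becomes known, with the best-guess rate still about 64%. A mix with small blocks such as 4, 6, 8 and 10 gives a similar fall in certainty but raises that rate to about 66%, so it is the poorer choice.

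The cost is one re-run of the program and a note to file. The largest possible imbalance in an unfinished block rises from five to six patients per stratum. Only patients randomized after the change are protected; with two to three blocks per stratum and recruitment under way since February 2017, that may be few. If recruitment has closed, the trial report should state who knew the block size and who booked patients.
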